## Methods

### Study Setting

This study will be conducted with the first-, second-, fourth-, and fifth-year undergraduate medical students enrolled in the Joint Medical Program (JMP) at the University of Newcastle and University of New England, Australia, which included 778 enrolled students in June 2021.

### Study Design

This study will adopt a 3-arm, parallel, partially blinded (participants), randomized controlled design.

All participants will complete a brief educational session that introduces the potential benefits of PF skills relating to burnout and well-being. Following this, they will be randomized into 1 of the 3 intervention arms using a 1:1:1 allocation ratio. Randomization will be conducted within the app. The three intervention arms are as follows: (1) individualized intervention, (2) nonindividualized intervention, and (3) waiting list. Figure 1 outlines the participants’ timeline for this study.

**Figure 1 figure1:**
[figure not shown]
Participant timeline.

### Sample Size

We conducted a power analysis to determine an appropriate sample size for a repeated measures multivariate analysis of variance (3 groups; measuring 2 time points [baseline and after the intervention]; high correlation between pre- and postintervention measures, 0.6). The calculation allowed for a small but still clinically meaningful effect size (0.25), given that this is the most conservative approach. For power of 80% and Cronbach α of .05, the total required sample size is 117 (39 per intervention arm). We allow for an attrition rate of up to 30% and set our target recruitment sample size at 153 participants (51 per intervention arm).

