As such, there are increasing calls by leading researchers for the use of individualized intervention methodologies, whereby an intervention is tailored to target the identified needs of each individual [40]. Individualized interventions can be delivered with a higher degree of precision than static interventions, providing the potential for superior efficacy and efficient resource allocation [74]. To address individual-level differences in this study, we will adopt a *treatment utility* methodology that compares an individualized version of the PF skills training app with a nonindividualized version [40]. Stage 1 of the intervention will deliver a static PF training module, and stage 2 will provide access to a library of short PF skills training activities that participants can access *on demand*. Participants receiving the individualized intervention will practice activities from the PF skill set that aligns with their identified needs during each training session, whereas those receiving the nonindividualized intervention will receive nontargeted training from any of the PF skill sets. This approach addresses individual differences in PF at the intervention level, allowing us to compare burnout and well-being outcomes between individualized and nonindividualized groups. A recent study using a similar methodological design demonstrated that an individualized version of a PF intervention was more effective than a nonindividualized version in reducing general psychological distress and improving mental health outcomes [75]. We expect that an individualized intervention will address the problem of individual heterogeneity by delivering more relevant and precisely targeted intervention skills than the nonindividualized version.

Hypothesis 3 states the following: we hypothesize that medical students in the individualized intervention group will demonstrate significantly greater improvements in PF, burnout, and well-being outcomes (before and after intervention) than those in the nonindividualized group.

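### The 0.25 effect size is called small and most conservative with no metric named; as Cohen's f, its likeliest meaning, it is medium, and the stated inputs do not give 117

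*Protocol article*

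**What the plan says.** The Sample Size section gives the trial's only power calculation. The test is a "repeated measures multivariate analysis of variance (3 groups; measuring 2 time points [baseline and after the intervention"), with a "high correlation between pre- and postintervention measures, 0.6". The effect size is described in one sentence: "The calculation allowed for a small but still clinically meaningful effect size (0.25), given that this is the most conservative approach". The result is: "For power of 80% and Cronbach α of .05, the total required sample size is 117 (39 per intervention arm"). An attrition allowance then raises the target to 153.

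The section does not say whether 0.25 is a standardised mean difference, Cohen's f or another index. It also does not say which effect is tested (group, time or their interaction) or how many dependent variables enter the multivariate test.

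Hypothesis 3, in the section on individual differences and intervention precision, compares two of the three arms: "we hypothesize that medical students in the individualized intervention group will demonstrate significantly greater improvements in PF, burnout, and well-being outcomes" than the nonindividualized group. No separate calculation is given for it.

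**The concern.** A reader who meets the words small and most conservative beside 80% power will conclude that the trial can detect a small difference between arms. If the three arms then look alike, that reader will treat a small benefit as largely excluded. Whether this is justified depends on the metric, which is missing, and on whether 117 follows from the printed inputs.

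Hypothesis 3 is where this matters most. Both app arms receive the same stage 1 and draw on the same stage 2 activity library, so their difference could well be smaller than that of either arm from the waiting list. A three-group omnibus power figure does not describe that contrast.

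**Working it through.** **Inputs (Sample Size section):** 3 equal arms, 2 time points, pre-post correlation ρ = 0.6, effect 0.25, 80% power, α = .05 (printed as Cronbach α, read here as the significance level), total N = 117.

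**Step 1. Is 0.25 a pairwise standardised difference?** The outcome SD is set to 1.
- The SD of a change score is √(2(1 − 0.6)) = 0.894. The baseline-adjusted SD is √(1 − 0.6²) = 0.8.
- Per-arm n ≈ 2(1.96 + 0.842)² × SD² / 0.25². This is 2 × 7.85 × 0.80 / 0.0625 ≈ 201 for change and 2 × 7.85 × 0.64 / 0.0625 ≈ 161 adjusted. The noncentral t gives 202 and 162.
- At 39 per arm the noncentrality is 0.25 / (SD × √(2/39)), which is 1.23 (change) or 1.38 (adjusted). Power is 23% or 28%.

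This reading is far from 39 per arm. Reading 0.25 as f² also misses, with a total of about 42. Cohen's f is the common scale whose variants lie on both sides of 117.

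**Step 2. What f = 0.25 means with three equal arms (between-groups convention).**
- One arm differs from two equal arms: f = d√2/3, so d = 0.25 × 3/√2 = 0.53 SD.
- Arms evenly spaced: f = d/√6, so the extreme arms differ by 0.25 × √6 = 0.61 SD and adjacent arms by 0.31 SD.

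Under the usual software convention for the within-between interaction, the same f corresponds to larger differences in change, 1.06 to 1.22 SD. By the usual benchmarks f = 0.25 is medium and f = 0.10 is small.

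**Step 3. Try to reproduce 117.** Noncentral F with 2 numerator df, and N − 3 denominator df (N − 4 when baseline-adjusted); f² = 0.0625.

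| Test | λ | λ at N = 117 | N for 80% (equal arms) | Power at 117 |
|---|---|---|---|---|
| Between-groups | 2f²N/(1 + ρ) | 9.14 | 127 (129) | 77% |
| Change score | f²N/[2(1 − ρ)] | 9.14 | 127 (129) | 77% |
| Baseline-adjusted | f²N/(1 − ρ²) | 11.43 | 102 (102) | 86% |
| Multivariate form without ρ | f²N | 7.31 | 158 (159) | 66% |
| Software-default interaction | 2f²N/(1 − ρ) | 36.56 | 35 (36) | over 99.9% |

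No row gives 117. The nearest match is the between-groups or adjusted formula at ρ = 0.5 (119, or 120 in equal arms), but the stated correlation is 0.6.

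**Step 4. Is 0.25 the most conservative choice?** A smaller f needs more participants. At f = 0.10 the total is 774 (between-groups or change), 620 (adjusted) or 196 (software-default interaction), each above 117.

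**Step 5. Hypothesis 3 at 39 per arm.**
- Detectable with 80% power: the noncentral t needs a noncentrality of about 2.838, so d/SD = 2.838 × √(2/39) = 0.643. This is 0.643 × 0.8 = 0.51 SD adjusted and 0.643 × 0.894 = 0.57 SD on change.
- If the arms are evenly spaced at f = 0.25, the Hypothesis 3 difference is 0.31 SD. The noncentrality is 1.51 (change) or 1.69 (adjusted), and power is 32% or 39%.
- If both apps work equally well, there is no Hypothesis 3 effect to detect. If the difference is 0.53 SD, power is 73% (change) or 82% (adjusted). At f = 0.25 that pattern requires the nonindividualized app to do no better than the waiting list, contrary to Hypothesis 1.

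**The case against.** The strongest reply is that the article condenses a fuller protocol and that 117 may rest on inputs it does not print. A Pillai-type multivariate test gives 117 with six outcomes on the between-groups or change scale, and about 113 with three outcomes if correlation and time are ignored. This stands as a possible explanation. It is not a reproduction, because neither count is stated, and it does not rescue the labels: the effect is still f = 0.25.

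Four stronger readings are tempting, and the documents do not support them.
- *That 0.25 can only be Cohen's f.* No metric is named. This is an inference from how badly the alternatives miss 117, and the SD equivalents depend on the convention used.
- *That 117 is too small.* It is too small against 129 or 159 and more than enough against 102 or 36. Failure to reproduce it does not show the omnibus test to be underpowered; on the between-groups or change test the shortfall is about 3 points.
- *That the protocol claims 80% power for Hypothesis 3, or would read a nonsignificant result there as no benefit.* It says neither. The Limitations section warns that low stage 2 engagement could hinder this comparison, although it does not mention sample size.
- *That Hypothesis 3 has 32% to 39% power.* That figure assumes evenly spaced arms, which the article does not state.

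**Conclusion.** The point holds as a misdescribed and unverifiable sample-size statement. On a pairwise scale, 0.25 is small but 39 per arm comes nowhere near 80% power. On the f scale, which is the plausible one, 0.25 is medium (0.53 to 0.61 SD between extreme arms on the between-groups convention) and is not the most conservative option. On neither reading does the design have 80% power for a small effect.

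The figure of 117 does not follow from the printed inputs under any of the standard variants tried, so the stated 80% cannot be confirmed in either direction. For Hypothesis 3 the finding is one of scope: the single omnibus calculation does not transfer to a two-arm contrast, which at 39 per arm has 80% power only for differences of about 0.51 SD or more.

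These results assume ρ = 0.6 as stated, equal arms, a common outcome SD, a two-sided .05 level for pairwise tests, and 39 analysed per arm.

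**What to change.** Revise the Sample Size paragraph and its reporting as follows.
1. Name the metric of 0.25 and the exact test and effect powered, including the number of outcomes if the test is multivariate.
2. Delete the words small and most conservative. If the metric is f on the between-groups convention, describe the effect as medium, about 0.5 to 0.6 SD between arms.
3. Replace 117, or the 80%, with what the named test gives at ρ = 0.6.
4. State the pairwise difference detectable with 80% power, including for Hypothesis 3, and say that a nonsignificant Hypothesis 3 result does not show that individualization has no benefit. A confidence interval for that contrast would make this plain.

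The cost is text only. The Results section reports that recruitment and data collection are complete, so enrolment does not change. The downside is that the stated figures will look less favourable.

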### Limitations

Although the study represents a rigorous and robust contribution to the existing literature, there are potential limitations. This study will assess the outcomes at baseline and following the completion of the intervention. This may not allow sufficient time for burnout or the well-being–related benefits of the intervention to manifest. As such, we intend to conduct subsequent follow-up studies with consenting participants to assess the long-term outcomes. As previously noted, early piloting of the intervention highlighted engagement issues regarding stage 2 of the intervention. Although we believe we have rectified these issues based on feedback from the pilot study, it is possible that participant engagement in stage 2 might be limited. This would hinder our efforts to assess the differences between individualized and nonindividualized versions. Additionally, the problem that we are seeking to address could further hinder engagement in this study, with stressed students potentially being less likely to maintain their participation over time. Early piloting suggests that short intervention components are a positive factor in facilitating intervention engagement among medical students but that time constraints might adversely impact the completion rates of postintervention outcome measures.

We anticipate that the intervention will produce positive outcomes, but there is a risk of the misuse of such findings. As previously noted, interventions empowering students and physicians to build psychological well-being should be incorporated into broader prevention initiatives that take steps to mitigate modifiable external burnout risk factors. However, organizations might overemphasize the role of individual interventions, placing the burden of burnout prevention solely on medical students and physicians. We advocate against the use of this type of training as a stand-alone intervention but rather as a component of a broader strategy that includes organizational-level changes where needed [29].

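### The recruitment target of 153 keeps the required 117 participants only up to 23.5% attrition, not the 30% the plan says it covers

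*Protocol article*

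**What the plan says.** The Sample Size section of the protocol article describes a power calculation for a "sample size for a repeated measures multivariate analysis of variance (3 groups; measuring 2 time points [baseline and after the intervention", with a "high correlation between pre- and postintervention measures, 0.6" and a "small but still clinically meaningful effect size (0.25". The targets are given as "For power of 80% and Cronbach α of .05"; the second term is evidently the significance level. From these, "the total required sample size is 117 (39 per intervention arm". The next sentence moves from the required number to the recruitment target: "We allow for an attrition rate of up to 30% and set our target recruitment sample size at 153 participants (51 per intervention arm".

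The article gives no other basis for 153 and no other attrition allowance. The Attrition section counts losses by stage, from enrolled students who never sign up to the app through to those who do not complete the T2 assessments. The Limitations section adds, as a possible risk, that "time constraints might adversely impact the completion rates of postintervention outcome measures".

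**The concern.** An attrition rate is a loss from those recruited. A target that allows for 30% attrition should therefore leave the required number after 30% of recruits have gone. The printed target looks as if 30% of the required number was added instead, and that is a smaller allowance.

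What is at stake is the link between the stated power and the stated attrition. Any attrition between 23.5% and 30% lies inside the range the plan says it covers, yet would leave fewer than the 117 it says it needs. A reader interpreting a null result would rely on that sentence to judge whether the trial kept its planned size. With only two assessment points, a missing T2 questionnaire has no later measurement to stand in for it.

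**Working it through.** **Inputs, all from the Sample Size section.** Required number 117 (39 per arm); attrition up to 30%; recruitment target 153 (51 per arm); power 80%; significance level 0.05; effect size 0.25; pre-post correlation 0.6; three groups, two time points.

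**1. Reproduce the plan's figure.** Adding 30% to the required number:
- total: 117 × 1.30 = 152.1, rounded up to 153 for three equal arms;
- per arm: 39 × 1.30 = 50.7, rounded up to 51.

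Both printed figures match. The article prints no formula, so this route is inferred from the match.

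**2. Apply the stated attrition to the stated target.**
- total: 153 × 0.70 = 107.1, about 107 retained;
- per arm: 51 × 0.70 = 35.7, about 36 retained;
- shortfall: 117 − 107 = 10, and 10/117 = 8.5% of the requirement.

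**3. Attrition that 153 does cover.** 1 − 117/153 = 36/153 = 23.5%. The target can lose 36 people, whereas 30% of 153 is about 46.

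**4. Target that would match the stated 30%.** 117 / 0.70 = 167.1, or 168 for equal arms (39 / 0.70 = 55.7, so 56 per arm). Check: 168 × 0.70 = 117.6, which keeps 117. This is 15 more than 153.

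**5. Effect on power, taking the plan's 80% at 117 as given.** For an F test with (2, N − 3) degrees of freedom and noncentrality λ = cN, 80% power at N = 117 requires c = 0.08455, so λ = 9.89. At N = 107, λ = 0.08455 × 107 = 9.05 and power is 76.0%. The loss is about 4 percentage points.

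**6. Absolute power under assumed tests.** The article does not say which effect in the repeated-measures analysis was powered, or on what scale 0.25 is measured. Assuming Cohen's f = 0.25 and ρ = 0.6:

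| Assumed test | λ | Power at 117 | Power at 107 |
|---|---|---|---|
| 3-arm test of change scores | f²N / [2(1 − ρ)] = 0.0781N | 76.6% | 72.4% |
| Baseline-adjusted ANCOVA | f²N / (1 − ρ²) = 0.0977N | 85.7% | 82.1% |
| Interaction, λ = f²N | 0.0625N | 66.4% | 62.1% |
| Interaction, λ = 2f²N / (1 − ρ) | 0.3125N | over 99% | over 99% |

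None of these gives exactly 80% at 117. They show how far absolute power depends on unstated choices. Steps 1 to 4 depend on none of them.

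**The case against.** The strongest reply is that little follows in practice. According to the Results section, recruitment ran in August and September 2021 and data collection ended in December 2021, so the target can no longer be acted on. The allowance is worded as an upper limit, and at 23.5% attrition or less the required 117 is kept. The error does not touch the outcomes, the planned mixed model or the validity of the comparison. All of this stands. It limits the consequence to a stated figure but does not make the figure right.

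A second reply is that the random-intercept mixed model in the Data Analysis section can keep participants who have only a baseline. That is true, but they have no post-intervention outcome and do not replace missing T2 data. The plan inflated its own number for attrition, so it treats 117 as the number needed after losses.

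A third reply is that 30% was meant as a mark-up on 117. The text calls it an attrition rate, and the Attrition section uses that word for people lost.

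Stronger readings that the article does not support:
- **Power falls from 80% to 72%.** The 72% comes from an assumed change-score test that gives 76.6%, not 80%, at 117. Setting it against the plan's 80% mixes the attrition slip with the separate question of how 117 was obtained, and doubles the loss.
- **80% power is certainly not reached at 107.** Under a baseline-adjusted ANCOVA with the same assumed inputs, 107 would still give 82%.
- **The plan expects poor T2 completion.** The Limitations section says this might happen and gives no rate.

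**Conclusion.** The stated figures contradict each other. With 30% attrition, 153 recruits leave about 107, 10 short of the 117 the same section requires; the target covers attrition only up to 23.5%. This is exact arithmetic on three printed numbers and rests on one reading, that attrition means loss from those recruited. A fuller protocol or an analysis plan could not reconcile the three.

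The power consequence is conditional. If 117 gives exactly 80% on a 2-df F test, 107 gives about 76%. Actual power at 107 could be lower or higher, because the test and the effect-size metric are not named. Whether 117 follows from its own inputs is a separate matter and is not decided here. The slip should be corrected because readers will rely on the sentence, but it is a misstated tolerance and not a flaw in the design or analysis.

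**What to change.** Keep 153 and restate the attrition sentence in one of two ways:
- *A target of 153 (51 per arm) retains the required 117 with attrition of up to 23.5%*; or
- *With 30% attrition, 153 recruits leave about 107 (about 36 per arm), with power of about 76% if 117 gives 80%.*

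If the second form is used, name the test and the effect-size metric behind the power figure, so that it can be reproduced. Raising the target to 168 is not proposed, since recruitment has closed.

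The cost is one sentence and a slightly less favourable stated tolerance or power. No extra participants are needed and the analysis does not change.

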### Eligibility

Participants will be eligible and included if they are enrolled in the first, second, fourth, or fifth year of the JMP at the University of Newcastle or enrolled in the first, second, fourth, or fifth year of the JMP at the University of New England and have regular access to a reliable internet connection and have regular access to an electronic device that is compatible with app use (smartphone or tablet). Third-year students will not be recruited for this trial, as this cohort was previously invited to participate in a pilot trial of the app intervention.

### Recruitment and Enrollment Procedures

Eligible students will be invited to participate in the study via the universities’ digital media and communication channels, including internal departmental mailing lists and e-newsletters, blackboard sites, and brief information sessions presented verbally by a researcher who is not connected with the JMP. Participation will be voluntary.

Students who are interested in participating will access the enrollment and consent page using a URL or QR code. The eligibility, consent, and enrollment processes will be conducted using REDCap (Research Electronic Data Capture; Vanderbilt University). Eligible participants should read the participant information statement on the web. Those who elect to participate will provide their consent via e-consent. Once consented and enrolled, participants will complete a brief demographic questionnaire, following which they will be assigned a unique participant ID and receive instructions for downloading the app. The app will be available for download through the App Store (Apple) and Play Store (Android).

### Data Collection Tools and Procedures

Data will be collected at two time points: T_1_ (baseline) and T_2_ (following the completion of the app-based intervention, commencing 5 weeks after baseline).

Study data will be collected via the app, which will record participant responses to questionnaires as well as app use data. Table 1 shows the administration time points for each outcome measure.

**Table 1 table1:** Outcome measures and administration time points.

Outcome	Assessment	Baseline (T_1_)	After the intervention (T_2_)	Every log-in (stage 2)
Demographics	Demographics	✓		
Burnout	Maslach Burnout Inventory–General Survey for Students	✓	✓	
Well-being	Mental Health Continuum–Short Form	✓	✓	
Psychological flexibility and psychological inflexibility	Multidimensional Psychological Flexibility Inventory–Short Form	✓	✓	
Depression, anxiety, and stress	Depression Anxiety and Stress Scale-21	✓	✓	
Current psychological flexibility difficulty	Check-in assessment			✓
Activity acceptability	Like or dislike			✓

